#### ***Secondary outcome measures***

Secondary outcomes will be time to delivery, gestational age at delivery, days on ventilation support, length of admission in neonatal intensive care, convulsions, apnoea, asphyxia, proven meningitis, pneumothorax, total days in hospital until 3 months corrected age. Furthermore we will examine differences in maternal mortality and maternal side effects leading to discontinuation of study medication.

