**Methods/Design:**

The Apostel III trial is a nationwide multicenter randomised controlled study. Women with threatened preterm labour (gestational age 25 – 34 weeks) defined as at least 3 contractions per 30 minutes, and 1) a cervical length of ≤ 10 mm or 2) a cervical length of 11-30 mm and a positive Fibronectin test or 3) ruptured membranes will be randomly allocated to treatment with nifedipine or atosiban. Primary outcome is a composite measure of severe neonatal morbidity and mortality. Secondary outcomes will be time to delivery, gestational age at delivery, days on ventilation support, neonatal intensive care (NICU) admittance, length admission in neonatal intensive care, total days in hospital until 3 months corrected age, convulsions, apnoea, asphyxia, proven meningitis, pneumothorax, maternal side effects and costs. Furthermore, an economic evaluation of the treatment will be performed. Analysis will be by intention to treat principle. The power calculation is based on an expected 10% difference in the prevalence of adverse neonatal outcome. This implies that 500 women have to be randomised (two sided test, β 0.2 at alpha 0.05).

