Studies on β adrenoceptor agonists have shown mixed results for postponing delivery compared to placebo [13]. As β adrenoceptor agonists have substantial side effects, use has been largely abandoned from clinical practice. A Cochrane review on calcium channel blockers for inhibiting preterm labour showed that nifedipine significantly reduced delivery within seven days of receiving treatment as compared with any other tocolytic agent (relative risk (RR) 0.76; 95% confidence interval (CI) 0.60 to 0.97) [14]. In addition, as compared to other tocolytics, calcium channel blockers also reduced the frequency of neonatal respiratory distress syndrome (RR 0.63; 95% CI 0.46 to 0.88), necrotising enterocolitis (RR 0.21; 95% CI 0.05 to 0.96), intraventricular haemorrhage (RR 0.59 95% CI 0.36 to 0.98) and neonatal jaundice (RR 0.73; 95% CI 0.57 to 0.93), and the requirement for women to have treatment ceased for adverse drug reaction (RR 0.14; 95% CI 0.05 to 0.36). The Cochrane review on oxytocin receptor antagonists for inhibiting preterm labour failed to demonstrate the superiority of atosiban over β adrenoceptor agonists (RR 0.98; 95% CI 0.68 to 1.41) or placebo (RR 2.5; 95% CI 0.51 to 12.35) in terms of tocolytic efficacy or infant outcomes [15]. On the other hand, atosiban is thought to be completely safe for the mother, whereas nifedipine may cause severe hypotension and fetal death [16]. Such side effects could however not be demonstrated in a previous nationwide study in The Netherlands [17]. Two small studies did not show a difference in effectiveness between nifedipine and atosiban [18,19], however, more side effects were observed with the use of nifedipine, consisting of hypotension, tachycardia headache and vertigo. Neonatal outcome was not reported in one study, the other study did not show a difference.

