Recently, a larger study was published, (n = 145) and found fewer failures within 48 hours for atosiban compared with nifedipine [20]. However, nifedipine was associated with a longer postponement of delivery. Neonatal morbidity was comparable between the two groups, although the number of neonatal admissions to the NICU and length of postnatal hospital admission was significantly higher in the atosiban group as compared with the nifedipine group. The main outcome measure of these 3 trials were tocolytic efficacy and tolerability, but the trails may be underpowered to detect clinically meaningfull effects in neonatal outcome. Therefore, the evidence remains inconclusive to support a balanced recommendation for clinical practice as the ultimate goal of tocolysis is not only to postpone delivery, but to improve neonatal outcome. This multicenter randomised clinical trial aims to compare nifedipine and atosiban in terms of neonatal outcome, duration of pregnancy, maternal side effects and costs. The study is conducted within the Dutch Obstetric Consortium, a collaborative effort of obstetric clinics in The Netherlands to perform clinical trials.

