## Methods/Design

### Aims

The objective of this study is to compare the effectiveness of the tocolytic agents nifedipine and atosiban in the improvement of neonatal outcome in women with threatened preterm labour with a gestational age between 25 – 34 weeks. Outcome is measured in terms of neonatal mortality and morbidity (chronic lung disease, severe intraventricular haemorrhage, periventricular leucomalacia, culture proven sepsis, necrotizing enterocolitis), gestational age at delivery, maternal side effects and costs.

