### Procedures, recruitment, randomization and collection of baseline data

The study will be a nationwide multicentre randomised controlled trial conducted within the Dutch Obstetric Consortium. The Dutch Obstetric Consortium is a research collaboration of obstetric clinics in the Netherlands. All 10 Dutch perinatal centres with NICU facilities will participate in the trial. In addition, 10 large teaching hospitals in the Netherlands and 2 perinatal centres in Belgium will participate in this trial.

Eligible women will be identified by the staff and/or local research coordinator of the participating hospitals. After counselling and reading the patient information form, patients will be asked for written informed consent. We will provide patient information in Dutch and English. After informed consent, baseline demographics, obstetric and medical history of patient will be entered in a web-based database, which will also facilitate randomisation. Randomisation will be performed by a web based computerized program using permuted-block randomisation. Randomisation allocation will be in a 1:1 ratio for Nifedipine or Atosiban, block size will be 4.

As this is a comparison of oral medication and intravenous medication, and as both group are treated with active medication, the study will not be blinded.

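### Maternal side effects are stated as an outcome without restriction, but the defined secondary outcome covers only those that end study medication

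*Protocol article*

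**What the plan says.** The maternal aim appears four times without any limit. Both the Background paragraph of the abstract and the closing paragraph of the main Background state it; the latter says the trial "aims to compare nifedipine and atosiban in terms of neonatal outcome, duration of pregnancy, maternal side effects and costs". The Aims section ends its list of outcomes with "gestational age at delivery, maternal side effects and costs". The abstract's own list of secondary outcomes ends with "asphyxia, proven meningitis, pneumothorax, maternal side effects and costs".

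The section Secondary outcome measures, where these outcomes are defined, is narrower. Besides maternal mortality it names only "maternal side effects leading to discontinuation of study medication".

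Three other statements bear on the point. The Background reports that in two small earlier comparisons of these drugs "more side effects were observed with the use of nifedipine, consisting of hypotension, tachycardia headache and vertigo". The section on procedures and randomisation says that "the study will not be blinded". The Interventions section describes scheduled blood pressure and heart rate checks for the nifedipine arm and mentions none for the atosiban arm.

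**The concern.** The article gives two different definitions of one secondary outcome, and the narrower one stands where the outcomes are defined. A woman who has a headache, a fast pulse or a fall in blood pressure and carries on with the drug belongs to the stated aim but not to the defined outcome. These are the effects that the Background singles out as differing between the drugs.

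The narrower outcome also adds a decision to the event. Whoever decides to stop knows which drug is being given, and the Background describes the two drugs' maternal safety in very different terms. A difference between arms in stopping could therefore reflect expectation as well as pharmacology.

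At stake is how the tolerability result can be read. If few women stop, little difference in discontinuation says little about how often side effects occurred. With two definitions in print, the choice between them could also be made after the results are known.

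**Working it through.** **1. The definitions side by side**

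| Place in the protocol article | Maternal side effects |
|---|---|
| Abstract, Background | compared, no restriction |
| Abstract, Methods/Design | secondary outcome, no restriction |
| Background, last paragraph | compared, no restriction |
| Aims | outcome, no restriction |
| Secondary outcome measures | only those that end study medication, plus maternal mortality |

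**2. Does another section fill the gap?**

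- Data analysis handles the remaining secondary outcomes in the same way as the primary outcome. It adds no maternal outcome.
- Follow-up of women and infants says that maternal assessments go into the web-based CRF. This concerns data capture and does not define an outcome.
- Data safety monitoring committee covers SAEs and SUSARs reported to that committee. This is oversight, and a non-serious headache or tachycardia would not be an SAE.

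No section makes a side effect that does not stop treatment a defined outcome to be compared between arms, beyond the unrestricted wording in the abstract and aims.

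**3. The article's own sample size, to fix the method**

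Inputs (Sample size; Abstract for the two-sided test): 25% v 15%, alpha 0.05, beta 0.2. With p̄ = 0.20:

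n per arm = [1.960·√(2·p̄·(1−p̄)) + 0.842·√(p₁(1−p₁) + p₂(1−p₂))]² / (p₁−p₂)²

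= [1.960·√0.32 + 0.842·√(0.1875 + 0.1275)]² / 0.10² = 249.98, so 250 per arm and 500 in total.

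The stated figure reproduces. It concerns the neonatal composite and does not decide this point.

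**4. Illustration of the information lost**

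The article gives no rates of maternal side effects or discontinuation for nifedipine against atosiban, so every rate below is an assumption. Power with n = 250 per arm, two-sided 5%:

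power = Φ{[|p₁−p₂|·√n − 1.960·√(2·p̄·(1−p̄))] / √(p₁(1−p₁) + p₂(1−p₂))}

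For 20% v 10%: (0.10·15.811 − 1.960·0.5050)/0.5000 = 1.183, so power is 88%.

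For 4% v 2% (1 in 5 of these stop): (0.02·15.811 − 1.960·0.2412)/0.2408 = −0.650, so power is 26%.

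| Assumed share of affected women who stop | 20% v 10% any side effect | 30% v 15% any side effect |
|---|---|---|
| all events counted | 88% | 98% |
| 1 in 2 | 56% | 76% |
| 1 in 5 | 26% (4% v 2%) | 37% (6% v 3%) |
| 1 in 10 | 15% (2% v 1%) | 20% |

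The table applies the same stopping share to both arms and a risk ratio of 2 throughout. If stopping differed more sharply, the result changes: an assumed 1% v 5% for discontinuation gives 75%. The table shows that a rarer outcome carries less information when the risk ratio is unchanged. It does not show what power this trial has.

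**The case against.** The other side has a good case on several points.

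- **The data may exist.** The abstract lists maternal side effects without restriction, maternal assessments are recorded in the CRF, and a journal article leaves the detail of the CRF to the full protocol. A reader might infer that most side effects will never be recorded. The article does not support that: it shows a narrow outcome definition and is silent on how wide the data collection is. This objection stands.
- **Who stops the drug.** A reader might infer that stopping is the physician's decision. The article does not say who decides, and the woman may do so. The weaker statement holds, because in an open trial both know the allocation.
- **Discontinuation is a legitimate endpoint.** The Background itself cites a review in which treatment stopped for adverse reactions separated calcium channel blockers from other tocolytics (RR 0.14; 95% CI 0.05 to 0.36). That comparison is not specific to atosiban, but it shows that the endpoint is in use and can discriminate. This is a reason to keep it, though not to let it stand for all side effects.
- **A wider count is not free of bias.** Reported headache or vertigo is open to expectation in an unblinded trial. With scheduled checks described only for nifedipine, hypotension and tachycardia may also be detected unequally. The article does not show which definition is less biased, so bias alone would not justify replacing one with the other.
- **The power figures rest on invented rates,** and the trial claims no power for maternal outcomes. This is correct, and they serve only as illustration.

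None of this removes the mismatch between the stated aim and the defined outcome.

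**Conclusion.** The point holds as an inconsistency with a practical consequence. The stated comparison covers all maternal side effects, and the defined outcome covers only those that end study medication. Followed as written, the definition excludes non-stopping events of the kind that the Background reports as differing between the drugs, and it rests on a decision taken with the allocation known.

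Its size in this trial cannot be established from the article. Under the assumed rates the loss of power ranges from moderate (98% to 76%) to severe (88% to 15%), depending on how many affected women stop. A reader might conclude that the tolerability question cannot be answered at all. That goes too far: it applies to the outcome as defined, and wider data may already be collected.

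The point is confined to one secondary outcome. The primary outcome, its analysis and the sample size of 500 are unaffected. It is still worth correcting, because the correction is cheap and closes a choice between definitions that could otherwise be made after the data are seen.

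**What to change.** Bring Secondary outcome measures into line with the aim by listing two separate maternal tolerability outcomes alongside maternal mortality:

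1. Any maternal side effect during study medication (hypotension, tachycardia, headache, vertigo, other), whether or not medication was stopped, recorded in the existing web-based CRF with the same items and in the same way in both arms.
2. Discontinuation of study medication because of side effects, as now.

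The abstract and Aims can then stay as they are. If the full protocol already contains the wider definition, correcting the outcome list is enough.

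The cost is a line in the outcome list, a short checklist if the CRF lacks one, and minor extra data entry. Identical recording reduces but does not remove the bias. Symptom reports remain open to expectation in an unblinded trial, and measured events remain open to unequal detection if vital signs are checked more often in one arm. The report should say so and interpret differences in these outcomes with caution. No change to the sample size or the primary analysis follows.

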### Follow-up of women and infants

All details of delivery, maternal and neonatal assessments during pregnancy and postpartum are recorded in a web-based Case Report Form (CRF). Details of neonatal admission are also recorded. Long-term follow up of children is dependent on future funding.

### Statistical issues

#### ***Sample size***

The sample size is calculated based on a 10%- reduction of the composite poor neonatal outcome from 25% in the atosiban arm to 15% in the nifedipine arm. With a beta of 0.2 and alpha of 0.05 we have to randomize 500 patients (250 in each arm).

#### ***Data analysis***

Data will be analyzed according to the intention to treat principle. The main outcome variable, ‘adverse neonatal outcome’, will be assessed by calculating rates in the two groups, relative risks and 95% confidence intervals as well as numbers needed to treat. To evaluate the potential of each of the strategies, we will also perform a per protocol analysis, taking into account only those women that were treated according to protocol. Time to delivery will be evaluated by Cox proportional hazards regression and Kaplan-Meier estimates, with account for differing durations of gestation at entry, and will be tested with the Log rank test. The other secondary outcome measures will be approached similarly to the primary outcome measure.

Furthermore, we plan to separately report on the treatment effect in the following subgroups: 1) PPROM versus intact membranes 2) GA < 30 weeks versus > 30 weeks, 3) fibronectin positive women only, 4) women with a cervix length < 10 mm, 5) multiple pregnancies, and 6) women with a history of preterm birth.

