## Background

Preterm birth is the most common cause of neonatal morbidity and mortality worldwide [1]. In the USA, the rate of infants born before 37 weeks gestation is 12-13%; while in Europe and other developed countries these rates vary between 5-11% [2,3]. Preterm birth accounts for approximately 75% of all neonatal deaths and 50% of childhood neurological morbidities [4,5] and puts a financial burden on the public health care system [6]. Neurodevelopmental impairments are frequently present in preterm infants, and are associated with gestational age [7]. Neonatal outcome is enhanced by antenatal corticosteroid administration and in-utero transfer to a tertiary care centre [8,9]. To optimize outcome in threatening preterm delivery, postponing delivery for 48 hours with tocolytic agents is common practice in most perinatal centres [10], to allow maximal effect of maternal steroid administration and transportation of the mother to a centre with neonatal intensive care unit (NICU) facilities.

Several types of tocolytic drugs are commonly used as treatment in preterm labour. These include the β adrenoceptor agonist ritodrine hydrochloride, the oxytocin receptor antagonist atosiban and the calcium channel blocking agent nifedipine. Several meta-analyses indicate that tocolytic drugs are superior to placebo or other tocolytics at delaying delivery by 48 hours and 7 days [11,12].

However, controversy exists as to which tocolytic is the drug of first choice. The ideal drug of choice should be efficient in postponing preterm labour, have a favorable safety profile in both mother and fetus, and should reduce neonatal morbidity and mortality at a reasonable cost.

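### The primary composite gets a crude comparison although gestational age at entry is known and varies from 25 to 34 weeks; a prespecified adjusted estimate could only help, at almost no cost

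*Protocol article*

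**What the plan says.** All references are to the protocol article.

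- **Primary outcome (Data analysis).** The composite "will be assessed by calculating rates in the two groups, relative risks and 95% confidence intervals as well as numbers needed to treat", by intention to treat. No covariate or stratification factor is named. Secondary outcomes other than time to delivery follow the same approach.
- **Time to delivery (Data analysis).** Cox regression, Kaplan-Meier estimates and a log rank test, "with account for differing durations of gestation at entry".
- **Subgroups (Data analysis).** Separate reporting is planned for gestation below and above 30 weeks, ruptured versus intact membranes, and multiple pregnancies, among others.
- **Entry range (Participants/eligibility criteria).** 25 to 34 weeks; singleton and twin pregnancies.
- **Randomisation (Procedures, recruitment, randomization and collection of baseline data).** "Randomisation allocation will be in a 1:1 ratio for Nifedipine or Atosiban, block size will be 4". No stratification by gestation is stated. Beforehand, "baseline demographics, obstetric and medical history of patient will be entered in a web-based database", and that same system performs the randomisation.
- **Sample size.** A fall "from 25% in the atosiban arm to 15% in the nifedipine arm", with "two sided test, β 0.2 at alpha 0.05" (Abstract), giving 500 women, 250 per arm.

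**The concern.** The entry window is nine weeks wide, and the composite is made up of complications that befall preterm infants. If risk depends on gestation at entry, part of the outcome variation can be explained by something known before randomisation. A crude comparison leaves that variation in the error term. Adjustment would then give a more precise estimate from the same 500 women.

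The plan brings gestation at entry into the analysis of one secondary outcome but not into the outcome on which the trial is sized. As far as the article states, the randomisation does not balance gestation either. The 30-week subgroup split describes the effect in two parts of the population; it does not sharpen the overall estimate.

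Timing matters as well. The trial is unblinded, so a covariate chosen after an imbalance has been seen would be open to challenge. It has to be named beforehand.

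**Working it through.** **1. Reproduce the plan's own figure.** Inputs from Sample size and the Abstract: p1 = 0.25, p2 = 0.15, two-sided alpha 0.05 (z = 1.960), power 80% (z = 0.8416), 1:1 allocation. With pooled variance, no continuity correction and mean risk 0.20:

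n per arm = [1.960·√(2·0.20·0.80) + 0.8416·√(0.25·0.75 + 0.15·0.85)]² / 0.10²
= [1.109 + 0.472]² / 0.01 = 249.98, rounded up to 250.

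The total is 500, exactly as stated. Power of the crude test at 250 per arm is 0.800.

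**2. Power after adjustment.** The documents give neither the distribution of gestation at entry nor its association with the composite. Both are therefore assumptions: entry uniform over 25 to 34 weeks, and a constant odds ratio (OR) per extra week. Intercepts were set so that the marginal risks stay at 25% and 15%. With 250 per arm and 6000 simulated trials per row, three tests were compared: crude, logistic regression with continuous gestational age, and Cochran-Mantel-Haenszel (CMH) stratified at 30 weeks.

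| Assumed OR per week | Control risk at 25 → 34 weeks | Crude | Adjusted, continuous | CMH at 30 weeks |
|---|---|---|---|---|
| 1.0 | 25% → 25% | 0.80 | 0.80 | 0.80 |
| 0.9 | 34% → 17% | 0.81 | 0.81 | 0.81 |
| 0.8 | 46% → 10% | 0.80 | 0.82 | 0.81 |
| 0.7 | 57% → 5% | 0.80 | 0.85 | 0.84 |
| 0.6 | 69% → 2% | 0.81 | 0.87 | 0.84 |
| 0.5 | 79% → 0.7% | 0.81 | 0.91 | 0.86 |

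The simulation error of each power is about √(0.8·0.2/6000) = 0.005, so the first two rows show no difference between the tests. Under the null, at ORs of 0.7 and 0.6, rejection rates for all three tests lay between 0.046 and 0.053. A split at 30 weeks recovers only part of the gain.

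**3. Does the gain carry over to the relative risk?** The logistic coefficient is a conditional odds ratio, whereas the plan reports a relative risk. A second simulation (4000 trials per scenario, same uniform entry) used logit slopes of −0.2, −0.3, −0.4 and −0.5 per week, that is ORs of about 0.82, 0.74, 0.67 and 0.61. Adjusted power was 0.812, 0.845, 0.854 and 0.869. The variance of the crude log relative risk exceeded that of the standardised one by factors of 1.03, 1.08, 1.16 and 1.20. So the marginal measure gains too.

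**4. Rough cross-check.** If the covariate explains a share R² of outcome variance, the effective size is about n/(1 − R²). For R² = 0.05, 0.10, 0.20 and 0.30 the power is 0.82, 0.84, 0.88 and 0.92; equivalently, 80% power needs 476, 450, 400 or 350 women. In the simulation, ORs of 0.8, 0.7 and 0.6 correspond to control-arm shares of 0.058, 0.131 and 0.225. The two agree closely at the lower end; the approximation is somewhat optimistic at the upper end.

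**5. Chance imbalance.** Under uniform entry the SD of gestation is 9/√12 = 2.60 weeks, so the between-arm difference in means has SD 2.60·√(2/250) = 0.23 weeks. At 20% overall risk and slopes of −0.2 to −0.5 per week, a 1-SD imbalance moves the crude risk difference by 0.7 to 1.5 percentage points. The crude standard error is √(2·0.20·0.80/250) = 3.6 points and already contains this component.

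**The case against.** The case against is substantial, and much of it stands.

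- **The crude analysis is valid.** It is an accepted intention-to-treat comparison, and the sample size was computed for it. A reader might infer that the trial loses power it was promised, or that its answer is biased. Neither follows: the planned 80% is delivered, and the crude confidence interval already allows for chance imbalance.
- **The strength of the predictor is not documented.** It is tempting to call gestational age the dominant predictor, with risk changing several-fold over the entry window. The documents do not say so. The Background remark that impairments "are associated with gestational age" concerns neurodevelopmental impairment, which is not in the composite. Delivery may also come well after entry, so gestation at entry may predict less well than gestation at birth.
- **Gestation is not ignored.** The 30-week subgroup is planned, as are subgroups for membrane status and multiple pregnancy. They do not make the overall estimate more precise, however.
- **The contrast with time to delivery is not a contradiction.** The wording there could mean a covariate, a stratum or delayed entry, and a time-to-event outcome may have its own reason for it. It shows only that the authors regard entry gestation as relevant.
- **An unseen analysis plan may add adjustment.** That is possible, and silence on detail would be no finding in a condensed article. But the article does state the primary analysis, and as stated it is crude. The point is a better method for that stated analysis.
- **Only gestational age was simulated.** Any benefit from also adjusting for plurality or membrane status is uncomputed.

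None of this removes the core: within simulation error, adjustment did no worse than the crude test in any scenario and better wherever gestation was materially prognostic.

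**Conclusion.** The point holds as a missed efficiency, not as an error. The stated analysis is sound and its sample size reproduces exactly.

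Prespecified adjustment for gestational age at entry would raise power at 500 women from 80% by anywhere between nothing and about 10 percentage points: to 82 to 87% at assumed odds ratios of 0.8 to 0.6 per week, and to 91% at 0.5. Type I error stays near 5%. These figures rest on uniform entry over 25 to 34 weeks, a constant odds ratio per week and the design risks of 25% and 15%; only the design risks come from the documents. If gestation at entry is weakly prognostic, as at 0.9 per week, the gain is negligible.

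The conclusion that adjustment is worth prespecifying does not depend on where in the range the truth lies, because the worst case costs essentially nothing.

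**What to change.** Before analysis, amend Data analysis so that the final primary analysis includes gestational age at randomisation as a continuous, prespecified covariate. Report a standardised (marginal) relative risk, risk difference and number needed to treat from logistic regression, or a modified-Poisson relative risk with robust standard errors. Either keeps the relative risk as the effect measure. Keep the crude rates and crude relative risk as supportive results.

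Singlet/twin status and membrane status may be added as prespecified covariates, with the caveat that their gain has not been computed.

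The interim look at 150 women would have about 75·0.25 + 75·0.15 = 30 events at the design rates. It can stay unadjusted or use gestational age alone.

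The cost is a few sentences of analysis wording, slightly more analysis work and a small dependence on the model. No extra women or visits are needed: gestation, plurality and membrane status all feature in the eligibility criteria and are known at entry.

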### Participants/eligibility criteria

We included women with a high risk of preterm birth. Women, aged ≥18 years, with threatened preterm labour and a gestational age between 25 and 34 weeks are eligible for participation in the Apostel III trial. The diagnosis of threatened preterm labour is defined by uterine contractions, at least 3 contractions per 30 minutes, and one of the following: 1) a cervical length of ≤10 mm or 2) a cervical length of 11-30 mm and a positive Fibronectin test or 3) ruptured amniotic membranes. Patients with singleton or twin pregnancies are eligible, independent of the position of the fetus.

Exclusion criteria are presence of a contra-indication for tocolysis (severe vaginal bleeding, signs of fetal distress or intrauterine infection, hypertension or use of anti-hypertensive medication, myocardial infarction (<1 month), unstable angina pectoris), cerclage, > 5 cm cervical dilatation, neonates suspected of chromosomal or structural anomalies and tocolytic treatment for >6 hours prior to arrival in a participating centre.

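### The subgroup plan leaves women at exactly 30 weeks unassigned, sets a cervix cut-point that does not match the entry criterion, and reports effects separately, with no stated comparator for four of six subgroups

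*Protocol article*

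**What the plan says.** After the main analyses, the Data analysis section states: "we plan to separately report on the treatment effect in the following subgroups". Six items follow.

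- Two items name both sides of a contrast: membrane status (PPROM or intact) and gestation, given as "GA < 30 weeks versus > 30 weeks".
- Four items name one group only: "fibronectin positive women only", "women with a cervix length < 10 mm", multiple pregnancies, and a history of preterm birth.

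Under Participants/eligibility criteria, the two entry routes based on cervical length are "a cervical length of ≤10 mm" and "a cervical length of 11-30 mm and a positive Fibronectin test". Ruptured membranes are a third route, with no cervical-length or fibronectin condition. The abstract gives the same entry limits.

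For the primary outcome, the Data analysis section plans rates, relative risks with 95% confidence intervals, and numbers needed to treat. It does not say how effects in different subgroups will be compared.

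**The concern.** There are two problems, and they do not depend on each other.

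**Cut-points.** Gestation is written as a two-way contrast, but a value inside the eligible range belongs to neither side. The short-cervix subgroup leaves out women with a cervix of exactly 10 mm, although the entry criteria place them in the short-cervix category. An analyst who follows the text drops or misassigns these women. An analyst who repairs it must choose a rule, possibly after seeing the data.

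**Method.** A separate estimate in each subgroup does not answer whether the effect differs between subgroups. That needs both levels of the factor and a comparison of the two effects. For four factors the second level is not stated. At this sample size, one stratum can easily have an interval that excludes no effect while the other does not, even if the true effect is the same in both. What is at stake is a statement that one drug is better at one gestation or membrane status but not at another, when the data cannot support it.

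**Working it through.** **1. The plan's own figure.** Inputs from Sample size: a fall "from 25% in the atosiban arm to 15% in the nifedipine arm", alpha 0.05, power 0.80. The abstract says two-sided.

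n per arm = [1.96·√(2·p̄·(1−p̄)) + 0.8416·√(p₁q₁ + p₂q₂)]² / (p₁−p₂)²

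Here p̄ = 0.20, so √0.32 = 0.5657. Also p₁q₁ + p₂q₂ = 0.1875 + 0.1275 = 0.315, so √0.315 = 0.5612.

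n = (1.1087 + 0.4723)² / 0.01 ≈ 250 per arm, 500 in total. This reproduces the stated size.

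**2. Women at exactly 30 weeks.** The article gives neither the distribution of entry gestation nor how age is coded. Assume a uniform distribution over 25 to 34 weeks, read as 9 weeks or 63 days.

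- Age in days, only 30+0 unassigned: 500/63 ≈ 8 women (1.6%).
- Age in completed weeks, all of week 30 unassigned: 500/9 ≈ 56 women (1 in 9).

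**3. Women at exactly 10 mm.**

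| Cervix | Entry category | Subgroup |
|---|---|---|
| below 10 mm | short cervix | in |
| exactly 10 mm | short cervix | out |
| 11–30 mm | needs positive fibronectin | out |

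This is not the same gap as at 30 weeks. The cervix item has only one stratum, so these women are left outside it and do not fall between two strata. The number affected cannot be estimated from the article.

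**4. Separate results under a uniform effect.** Assume the true rates are 25% and 15% in every woman, and that a factor splits the trial in two. The article gives no subgroup shares, so the splits are assumptions.

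Power = Φ[(0.10·√n − 1.1087) / 0.5612], with n per arm in the stratum.

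- Equal split, n = 125: (1.1180 − 1.1087)/0.5612 = 0.017, power 0.507. Exactly one of two significant: 2 × 0.507 × 0.493 = 0.50.
- 30/70 split, n = 75 and 175: power 0.333 and 0.649. Exactly one significant: 0.333 × 0.351 + 0.649 × 0.667 = 0.55.
- 20/80 split: power 0.237 and 0.707. Exactly one significant: 0.237 × 0.293 + 0.707 × 0.763 = 0.61.

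**5. What an interaction estimate can deliver.** Equal split, planning variances in both strata.

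- Risk-difference scale: SE = √(2 × 0.315/125) = 0.071. Power for a 10-point difference between strata: Φ(0.10/0.071 − 1.96) = 0.29. Difference detectable with 80% power: 2.80 × 0.071 ≈ 0.20, or 20 points.
- Relative-risk scale: the variance of log RR in one stratum is (0.75/0.25 + 0.85/0.15)/125 = 0.0693. The SE of the log ratio of two relative risks is √(2 × 0.0693) = 0.372. The 95% interval runs from the estimate divided by e^(1.96 × 0.372) ≈ 2.07 to the estimate times 2.07.

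**The case against.** The strongest reply is that this is one sentence in a condensed article. Interaction analysis is commonly left to the full protocol or the statistical analysis plan, and neither is shown. A reader might infer that no interaction comparison will be made. The article does not say so, and its silence does not establish it. That part of the reply stands.

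A reader might also infer that chance differences will be presented as effect modification. The article states no such rule of interpretation, so this is a risk and not a planned error. Nor do the cut-points create spurious effect modification. They leave women unassigned or misclassified, which is a different fault.

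The power figures describe any two-way split of a trial of this size. The article plans relative risks with confidence intervals, and the only test it names is the log-rank test for time to delivery. That is fair. The figures still apply to anyone who checks whether each stratum's interval excludes 1, because that is in effect a test.

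It would be too strong to say that effects cannot be compared for the four single-group items. For multiple pregnancy and previous preterm birth, the complement is the rest of the trial. For cervix and fibronectin it is less clear, because women with ruptured membranes can enter without either measurement.

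The reply does not cover the cut-points. An analysis plan can add what an article omits, but the stated limits are faulty as they stand: one leaves a gap and the other does not match the entry criterion.

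**Conclusion.** The point holds as two separate, modest defects in the stated subgroup plan. The primary analysis and the total of 500 are unaffected.

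The cut-point defects can be read directly from the text. The gap at 30 weeks affects about 8 to 56 of 500 women, depending on how age is coded, if entry gestation is uniform. The effect of the 10 mm mismatch is unknown and may be small.

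The method defect is that separate effects, with four of the six subgroups lacking a stated comparator, cannot show whether effects differ. With a uniform 25% v 15% effect, exactly one of two strata would be significant in about 50% of trials for an equal split, and in 55% or 61% for 30/70 or 20/80 splits. These shares are assumptions. The documents do not support the stronger claim that an interaction comparison has been ruled out.

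**What to change.** Before analysis, in the protocol or the statistical analysis plan:

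1. Set the gestation strata to <30 v ≥30 weeks, and say whether age is in days or completed weeks.
2. Set the short-cervix subgroup to ≤10 mm, to match the entry criterion.
3. Name the complement for each single-group factor:
   - twin v singleton;
   - previous preterm birth v none;
   - cervix ≤10 mm v >10 mm among women measured;
   - fibronectin positive v negative among women tested.

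   Show unmeasured and untested women separately. A split of ≤10 v 11–30 mm would leave out women with ruptured membranes who have a longer or unmeasured cervix. Positive against all others would mix negative with untested women.
4. For each of the six factors, report the relative risk in both strata and the treatment-by-factor interaction, as a ratio of relative risks with its 95% confidence interval.
5. Base any subgroup statement on that interaction, and label all six subgroups exploratory.

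The cost is wording and a few lines of analysis, with no change to sample size or trial conduct. Whether cervical length and fibronectin were recorded in women with ruptured membranes should be checked. The downside is imprecision: about 29% power for a 10-point difference between equal strata. A wide interval must therefore not be read as evidence that the effect is the same.
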